## Abstract

**Background:**

High blood pressure is an independent risk factor of cardiovascular disease (CVD) and is a major cause of disability and death. Managing a healthy lifestyle has been shown to reduce blood pressure and improve health outcomes. We aim to investigate the effectiveness of a lifestyle modification intervention program for lowering blood pressure in a rural area of Bangladesh.

**Methods:**

A single-center cluster randomized controlled trial (RCT). The study will be conducted for 6 months, a total of 300 participants of age 30 to 75 years with 150 adults in each of the intervention and the control arms. The intervention arm will involve the delivery of a blended learning education program on lifestyle changes for the management of high blood pressure. The education program comprises evidence-based information with pictures, fact sheets, and published literature about the effects of high blood pressure on CVD development, increased physical activity, and the role of a healthy diet in blood pressure management. The control group involves providing information booklets and general advice at the baseline data collection point. The primary outcome will be the absolute difference in clinic SBP and DBP. Secondary outcomes include the difference in the percentage of people adopting regular exercise habits, cessation of smoking and reducing sodium chloride intake, health literacy of all participants, and the perceived barriers and enablers to adopt behavior changes by collecting qualitative data. Analyses will include analysis of covariance to report the mean difference in blood pressure between the control and the intervention group and the difference in change in blood pressure due to the intervention.

**Discussion:**

The study will assess the effects of physical activity and lifestyle modification in controlling high blood pressure. This study will develop new evidence as to whether a simple lifestyle program implemented in a rural region of a low- and middle-income country will improve blood pressure parameters for people with different chronic diseases by engaging community people.

**Trial registration:**

ClinicalTrials.gov NCT04505150. Registered on 7 August 2020

## Background

High blood pressure is one of the fundamental causes of cardiovascular disease (CVD) and a major cause of disability and death. Raised blood pressure accounts for as many as 10.4 million deaths per year globally [1, 2]. The prevalence of high blood pressure has increased from 87.0 million in 1999–2000 to 108.2 million in 2015–2016 [3]. The estimated number of annual deaths is 1.5 million worldwide, of which 9.4% has been reported to be due to high blood pressure [1]. Modifiable risk factors such as smoking, unhealthy diet, and physical inactivity are shared and established risk factors for CVDs [2, 4]. Different strategies including lifestyle changes such as smoking cessation, diet alteration including a reduction in dietary sodium intake, increased physical activity, and adherence to medication can help in managing high blood pressures and improve health outcomes by decreasing or slowing complications associated with high blood pressure and other CVDs [4–8], but strategies targeting multiple-level or patient-level barriers are effective in controlling high blood pressure [9].

Development and subsequent evaluation of effectiveness for any intervention targeting high blood pressure should include core components comprising baseline participant assessment, educational interventions for participants to acquire adequate knowledge about the etiology and risk factors of hypertension, and modification of lifestyle factors such as participating in regular physical activity, consuming a healthy diet, and smoking cessation [10]. One of the successful models in increasing hypertension awareness, control, and treatment is the Canadian Hypertension Education Program (CHEP), which has been recommended for the development and implementation of healthcare system at the international level [11, 12]. Despite the high prevalence of high blood pressure in low-income and middle-income countries, there are relatively few data on intervention programs from low-income and middle-income countries (LMICs) [13]. Studies also report that a significant proportion of people with high blood pressure are undiagnosed or do not meet targets to control blood pressure both in developed [14] and in LMICs [15, 16]. Among people with known high blood pressure, less than one-third of people can control their high blood pressure with appropriate treatment [13, 17]. Lifestyle modification programs have been shown to be effective in controlling blood pressure in LMICs [18–20].

Bangladesh, a low-income country in South East Asia, is currently confronting an increasing burden of chronic diseases, including high blood pressure [21]. Islam et al. conducted a cross-sectional study among adults age ≥ 30 years in a rural district in Bangladesh that reported the knowledge, attitudes, and practice of diabetes [22] and common eye diseases [23], and found overall knowledge was below average. The study also reported the prevalence and risk factors associated with known and undiagnosed diabetes [24] and self-reported known high blood pressure and newly diagnosed high blood pressure [15]. The study identified that 40% of adults had stage 1 high blood pressure with a cut-off of systolic blood pressure (SBP) ≥130 mmHg or diastolic blood pressure (DBP) ≥80 mmHg or taking antihypertensive [25], of which 82% were previously undiagnosed [15]. Almost 60% of those with high blood pressure also had diabetes [24].

Recently, a community-based cluster randomized controlled trial was conducted in rural communities in Bangladesh, Pakistan, and Sri Lanka. This multicomponent intervention program was conducted for 24 months in 2645 adults with hypertension defined as blood pressure greater than or equal to 140/90 mmHg. The study reported a statistically significant mean reduction of SBP of 5.2 mmHg from the baseline mean blood pressure 146.7 mmHg compared to the usual care in which the reduction was 3.9 mmHg. A similar mean reduction in SBP was observed in a previous cluster randomized clinical trial. Therapeutic lifestyle change intervention plus motivational interviewing intervention for 6 months was associated with SBP reduction of 5.79 mmHg compared to health education intervention only [26]. Relatively small reductions of 2 mmHg in SBP and DBP have been reported to lower the risk of stroke by 14% and 17%, respectively, and the risk of coronary artery disease by 9% and 6%, respectively [27]. The intervention program included home visits by government community health workers for blood pressure monitoring and counseling and the training of physicians [20]. A possible limitation of this intervention program [20] may be that home visits by trained community health workers for blood pressure monitoring and counseling may not be a sustainable and cost-saving approach due to the shortage of qualified workforce and the budget constraints in low-middle-income countries. Application of blended learning education programs to educate patients in managing blood pressure by changing lifestyle and participation in intervention programs as volunteers coordinated by volunteer leaders may be a sustainable approach for lowering blood pressure in the community setting. The goal of this study is to compare a multicomponent intervention program to evaluate its effectiveness for lowering blood pressure among adults with high blood pressure in a rural district in Bangladesh.

Health literacy is a complex and combined perception comprising a range of attributes including available resources of health-related information and an individuals’ intellectual, emotional, social, and personal skills [28]. Health literacy empowers people with skills to improve their health and well-being. Evidence indicates that deficits in health literacy are associated with poorer health outcomes and higher health-related costs at both individual and system levels [29, 30]. Improved health literacy had been reported to be associated with reductions in risk behaviors for chronic disease [31, 32]. However, an extended and often asymptomatic onset and a need for ongoing management, these conditions present people with a sharp and upward learning curve about risks, treatments, and self-care. Self-care, especially in resource-limited settings, an essential dimension of treatment, depends on the ability of systems and providers to teach and patients to learn effective self-management skills [33]. At the individual level, good health literacy is the foundation of successful management and prevention of chronic disease. Health literacy assessment can be used to improve community participation in health, health service planning, public health education, and policy development [34]. In the past decade, much research on the impact of health literacy on health outcomes has been conducted across the globe [32, 35]; however, health literacy tools in rural areas of Bangladesh have not been developed or tested. The European Health Literacy Survey (HLS-Q12) questionnaire has been used to assess health literacy [36]; however, its usefulness to measure health literacy in rural Bangladesh has not been investigated.

### Aim of the study

The aim of this study is to investigate if a health education intervention program lowers high blood pressure.

### Primary objective and hypothesis

#### Objective 1

To assess the effectiveness of a health education program to adopt lifestyle modification in managing systolic and diastolic blood pressure.

#### Hypothesis

A motivational education program to change lifestyle by smoking cessation, taking part in regular physical activities and managing a healthy diet, and receiving a weekly motivational phone call will reduce blood pressure compared to the control group receiving an information booklet and general advice only.

### Secondary objectives related to the intervention

*Objective 1*: To report the difference in the proportion of people adopting regular exercise habits, cessation of smoking, and adopting healthy dietary habits between control and intervention groups

*Objective 2*: To report the general health literacy among the total study participants

*Objective 3*: To report the willingness to receive and pay for a text message system for lifestyle modification

*Objective 4*: To report the perceived barriers and enablers in participating and adopting lifestyle modifications to manage blood pressure

## Methods

Study design: a single-center, cluster randomized control trial (RCT). Control:intervention = 50%:50%

### Duration

Six-month trial

### Participants

The study will be conducted in the Banshgram Union of Narail district, located approximately 200 km southwest of Dhaka, Bangladesh. To understand the location, Bangladesh is a country of over 163 million people divided into 64 districts. Each district is divided into Upazilas (sub-districts), and each Upazila is divided into Unions which consist of 15–20 villages [37]. A cross-sectional study was conducted among 3104 participants of age 30–89 years in 2013 in the Banshgram Union that identified 1242 (40%) participants with hypertension according to WHO guidelines as SBP ≥140 mmHg and/or DBP ≥90 mmHg and/or self-report use of medication for hypertension [15]. Given the intervention of the present study that needs lifestyle modification and more use of a mobile phone, it was decided to limit the age to 75 years as access and use of mobile phones was likely more problematic with older participants [38]. Thus, we chose to limit our upper age to 75 years, leaving 1072 eligible participants for this study. Based on power calculations, we require only 300 participants and expect to recruit the required number of participants without any major difficulty. Inclusion criteria will be based on recent guidelines or definition of hypertension [25]; anyone with SBP ≥130 mmHg and/or DBP ≥80 mmHg and/or self-report use of medication for hypertension will be considered eligible for the current study.

### Sample size

A total of 212 participants (106 per group) will provide 95% power at a significance level of 0.01 to detect a difference of 5 mm/Hg in SBP, assuming a standard deviation of 12 mm/Hg. Assuming loss-to-follow of approximately 40% for various reasons, the required number to recruit is 300 participants (150 per group). This sample size was based on previous research, which showed a decrease in SBP of 5 mm/Hg was associated with a clinically significant reduction in the relative risk of stroke and coronary heart disease events [39].

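### The Sample size section's 95% power at significance level 0.01 with 106 per group is wrong for the planned between-arm comparison; the stated inputs give about 67% (two-sided, unadjusted, clustering ignored)

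*Protocol article*

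**What the plan says.** The Sample size section of the protocol article gives one calculation: "A total of 212 participants (106 per group) will provide 95% power at a significance level of 0.01 to detect a difference of 5 mm/Hg". The outcome concerned is SBP, and the spread enters as "assuming a standard deviation of 12 mm/Hg". The section then allows for loss to follow-up of about 40% and arrives at 300 recruits, 150 per group. It does not say whether the test is one- or two-sided, and gives no formula, baseline/follow-up correlation, intracluster correlation or design effect.

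The Participants section relies on the result: "Based on power calculations, we require only 300 participants". Allocation is equal (Methods: "Control:intervention = 50%:50%").

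The comparison to be powered is between arms. The Hypothesis section expects blood pressure to fall relative to the control group. The Statistical analyses section defines the effect as the difference between the change in the control group and the change in the intervention group, analysed on individual data. The Primary outcome section mentions differences both within and between groups. The Cluster randomization and Sequence generation sections divide 18 villages into two clusters of nine, make the cluster the unit of randomisation, and allocate by a coin toss.

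**The concern.** For a standardised difference of 5/12 ≈ 0.42, 106 per arm is too few for 95% power at so strict a significance level. It is about half the usual two-sample answer, which suggests that the variance of the second arm was left out.

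This is the trial's only justification of its size, and the same section ties 5 mmHg to a clinically significant reduction in risk. A reader who takes the claim at face value could treat a non-significant result as strong evidence against a 5 mmHg benefit. On the stated inputs, the test would miss a true 5 mmHg difference about one time in three, before any loss of power from clustering.

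**Working it through.** **Inputs (Sample size and Methods sections).** Difference δ = 5 mmHg; SD σ = 12 mmHg; α = 0.01; power 95%; n = 106 per group; 1:1 allocation. Sidedness is not stated, so both are tried. Normal quantiles: 2.576 (two-sided 0.01) and 1.645 (95% power).

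**1. Try to reproduce the plan's figure as a two-sample comparison.**
- Required n per arm = 2(2.576 + 1.645)²(12/5)² ≈ 205.2, so 206. The noncentral t calculation gives 207 (206 gives 94.9%, 207 gives 95.0%). The total is 414 evaluable.
- With 106 per arm, the standard error is 12√(2/106) = 1.648 and the noncentrality is 5/1.648 = 3.03.

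| Test, 106 per arm | Power (t) | Power (normal) |
|---|---|---|
| two-sided 0.01 | 66.8% | 67.6% |
| one-sided 0.01 | 75.4% | 76.0% |
| two-sided 0.05 | 85.5% | 85.9% |

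None of these gives 95%. The difference detectable with 95% power at two-sided 0.01 is 4.221 × 1.648 ≈ 6.96 mmHg.

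**2. Find what does give 106.** A one-sample or paired t-test with the same inputs needs (2.576 + 1.645)²(12/5)² ≈ 102.6 by the normal approximation. By noncentral t, n = 105 gives 94.8% and n = 106 gives 95.0%, so 106 is the exact minimum. Doubling it gives 212.

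**3. Read 12 mmHg as the SD of change.** The two-sample formula is unchanged, so power stays at 66.8%.

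**4. Read 12 mmHg as the raw SD and adjust for baseline (ANCOVA).** 95% power with 106 per arm needs a residual SD of 5/(4.221 × √(2/106)) ≈ 8.62. Setting 12√(1 − ρ²) = 8.62 gives ρ ≈ 0.70. Correlations of 0.5 and 0.6 give about 82% and 88%. These correlations are assumptions; the article gives none. For an unadjusted analysis of change, 12√(2(1 − ρ)) = 8.62 gives ρ = 1 − 74.4/288 ≈ 0.74.

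**5. Use the recruited number.** At two-sided 0.01 (noncentral t):
- no loss, 150 per arm: 84.4%;
- 40% loss, 150 × 0.6 = 90 per arm: 57.7%.

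A 40% loss from 300 leaves 180, not 212. Keeping 212 after 40% loss would need 212/0.6 ≈ 354, whereas 212 × 1.4 ≈ 297, which is close to the stated 300.

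**6. Clustering.** Nothing in the calculation allows for it. Any positive between-cluster variance increases the variance of the treatment contrast, so every figure above is an upper bound for its own reading. With one randomised block per arm, that variance cannot be separated from the treatment effect. The article gives no intracluster correlation, so no clustered power is computed here.

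**The case against.** **The 67% is not a ceiling under every reading.** A reader might infer that power is 67% at best. The article does not support that. Sidedness is not stated, and a one-sided test gives 75%. The Abstract names analysis of covariance, so baseline adjustment is part of the plan; if 12 mmHg is the raw SD, adjustment raises power and could reach 95% at a correlation of about 0.70. This stands, and the 67% must carry its labels. It does not validate the claim, because the Sample size section states neither an adjusted SD nor a correlation.

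**The within-group part of the outcome.** The Primary outcome section includes within-group change, and 106 per group is a correct one-sample answer for that. But a before-after change in one arm cannot test the stated hypothesis, which is against the control group.

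**The origin of 106 is an inference.** The match is exact on every stated input, but no formula is named. It should be described as the likely source, not as fact.

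**A village-based clustered power.** A reader might put a figure on the clustering loss with a village design effect and 16 degrees of freedom from 18 villages. The article does not support this: villages are not randomised individually; two nine-village blocks are. Such a figure would describe a different trial and would hide the one-block-per-arm problem.

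**Timing.** The article gives recruitment as December 2020 to March 2021, so a correction may not change the number enrolled. It still changes how the result can be read. An analysis plan that is not shown does not cure this either, since the point is a wrong figure in the article, not an omission.

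**Conclusion.** The point holds. As written, 95% power at 0.01 with 106 per group is wrong for the between-arm comparison. On the stated difference and SD, and assuming a two-sided unadjusted two-sample test with independent participants, power is about 67%, and 95% needs about 207 per arm, close to twice the stated number. The evaluable number implied by the article's own loss assumption is lower still, at 90 per arm and about 58%. No reading that uses only the stated inputs recovers 95%.

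The conclusion does not depend on how 106 was obtained or on any assumed intracluster correlation. Clustering can only lower the figures, by an amount the design cannot estimate. It does not follow that the trial must enrol more people; what fails is the power statement.

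**What to change.** In the Sample size section:
- Delete the claim of 95% power at a significance level of 0.01.
- State the significance level and sidedness to be used in the analysis, then give either the two-sample power for 5 mmHg or the detectable difference, for the evaluable number expected after loss (90 per arm if 40% loss is kept).
- Say whether 12 mmHg is the SD of a single measurement, of change, or after baseline adjustment. If baseline adjustment is relied on, state the assumed correlation and its basis.
- Say that the figure ignores between-cluster variation, which two randomised clusters cannot estimate, and is therefore an upper bound. Do not substitute a calculation that treats 18 villages as randomised.
- Make the sentence in the Participants section that relies on the power calculation consistent with the new text.

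The cost is rewording one paragraph and one sentence. The stated power becomes less favourable. No participants are added and enrolment is unchanged.

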### Recruitment

Recruitment will be conducted by the investigators of the Organization for Rural Community Development (ORCD) in Bangladesh (www.orcdbd.org). The ORCD is a local non-government organization involved in providing health services to rural people and conducting research. The ORCD investigators, and trained data collectors, will communicate with the potential participants over the telephone or by direct contact. The ORCD participants are not involved in the study design, but they will be involved in the recruitment and conduct of the study. Upon establishment of contact with eligible participants, the baseline data collection will be done through household visits. At household visits, the ORCD investigators and the data collectors will briefly explain the study objectives and their voluntary participation in the project. Interested potential participants will be assessed for eligibility that includes the measurement of blood pressure. Informed written consent will be obtained from all participants. Upon enrolment, a face-to-face interview will be conducted to collect information and record blood pressure from the participants whilst maintaining a social distance. Recruitment will stop once the required number of participants are enrolled. If we are unable to recruit completely from the original cohort, we will expand and recruit participants from outside of this specific cohort but from the exact location. Recruitment from outside of the proposed cross-sectional cohort is not expected to affect the primary objectives. Our source population is over 1000 participants. We do not anticipate any problems in recruiting 300 participants.

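### With the assumed 40% loss to follow-up, 300 recruits leave 180 evaluable participants, not the 212 that the sample-size section says it needs

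*Protocol article*

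**What the plan says.** The Sample size section of the protocol article gives three linked figures.

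- **Evaluable target:** "A total of 212 participants (106 per group) will provide 95% power at a significance level of 0.01". The planning inputs behind it are a between-group gap of 5 mmHg in systolic pressure and an SD of 12 mmHg.
- **Loss and recruitment:** "Assuming loss-to-follow of approximately 40% for various reasons, the required number to recruit is 300 participants (150 per group".

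The recruitment figure is the operating target. The Abstract, Participants, Recruitment and Cluster randomization sections all repeat it, as 300 in total or 150 per arm or cluster. The Recruitment section adds: "Recruitment will stop once the required number of participants are enrolled". No other loss rate appears in the article, and nothing redefines the 40% as a mark-up on the evaluable number.

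**The concern.** A loss rate applies to the people enrolled, so the number to recruit is the evaluable target divided by the fraction retained. The plan's 300 is too small for that. It is close to what results from adding 40% of the evaluable target to itself, a common slip.

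If the stated loss occurs, the trial ends below its own evaluable target even though recruitment went exactly to plan, and the stated power then does not describe the trial that was planned. A reader also cannot tell whether the design rests on 212 or 180 evaluable participants, or on 29% or 40% loss. This section is the only sample-size justification in the article.

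**Working it through.** **Inputs, all from the Sample size section:** 212 evaluable (106 per group), loss about 40%, 300 recruited (150 per group), difference 5 mmHg, SD 12 mmHg, significance level 0.01, power 95%. The section does not say whether the test is one- or two-sided; two-sided is used here unless noted.

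**Step 1. Where 300 may come from.** 212 × (1 + 0.40) = 296.8, which is 297 and rounds up to 300. The section shows no formula, so this is an inference.

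**Step 2. Correct inflation.** 212 / (1 − 0.40) = 353.3, so 354 recruits (177 per group).

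**Step 3. What 300 delivers.** 300 × 0.60 = 180, or 90 per arm. The shortfall is 212 − 180 = 32, and 32/212 = 15%.

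**Step 4. Loss that 300 can absorb.** 1 − 212/300 = 29.3%.

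**Step 5. Does the word approximately help?** At 38% loss, 300 leaves 186, and 342 recruits would be needed. At 42%, it leaves 174, and 366 would be needed. Neither comes near 212.

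**Step 6. Effect on power of this step alone.** Exact noncentral t calculations, difference 5, SD 12, two-sided 0.01:

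| Basis | Noncentrality | n = 106 | n = 90 | Change |
|---|---|---|---|---|
| One-sample or paired | (5/12)√n | 95.0% | 90.4% | about 5 points |
| Two-sample, n per arm | 5 / (12√(2/n)) | 66.8% | 57.7% | about 9 points |

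The first row reproduces the plan's own figure: 106 is where a one-sample or paired test first reaches 95% (94.8% at 105, 95.0% at 106). The second row is the between-group comparison that the trial actually makes.

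At two-sided 0.05, the two-sample power with 90 per arm is 79.4%. A one-sided 0.01 test does not rescue the claim either: two-sample power is 75.4% at 106 per arm and 67.3% at 90.

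**Step 7. Splitting the gap to 95%.** For a two-sample test at two-sided 0.01, the distance from 95% to 57.7% is about 37 points. About 28 of them (95 − 66.8) are already lost at 106 per arm, before anyone drops out. About 9 (66.8 − 57.7) come from the loss allowance.

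**The case against.** Four counter-arguments deserve a hearing.

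- **The 40% may be a mark-up, or only approximate.** The text calls it loss to follow-up, and step 5 shows that a reasonable band around 40% does not reach 29%. This does not stand.
- **The detail may belong to a fuller document.** Nothing is missing here. All three figures are printed, and they are inconsistent with each other. This does not stand either.
- **The effect on power is modest.** This stands. A reader might infer that the loss slip takes power from 95% down to 58%. The figures do not support that. The isolated cost is about 5 points on the basis that reproduces 106, or about 9 points for a two-sample test. The larger loss arises because 106 per group is wrong for a between-group comparison, which is a separate defect.
- **Clustering is a different matter.** This also stands. A reader might want to go further and quote power for 18 villages with an assumed intracluster correlation. The Cluster randomization and Sequence generation sections describe two clusters of nine villages, with the intervention cluster chosen by a coin toss. Villages are not the randomised units, and the article gives no intracluster correlation. Such figures would not describe this design and form no part of this point.

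**Conclusion.** The point holds as an arithmetic contradiction within one section. With about 40% loss, 300 recruits give 180 evaluable participants (90 per arm), 15% below the stated 212. Keeping 212 would take 354 recruits, and 300 is enough only if loss stays at or below about 29%. This conclusion needs nothing beyond the article's own three numbers.

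The power consequence rests on the stated difference and SD and on a two-sided 0.01 test. It is 95.0% to 90.4% on the one-sample or paired basis, or 66.8% to 57.7% for a two-sample comparison before clustering. The stated 95% therefore fails on either basis once 40% are lost, but most of the two-sample gap should not be charged to this error.

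**What to change.** Keep 300 and the 40% assumption, and rewrite the end of the Sample size section to state that 180 evaluable participants (90 per arm) are expected. Replace the 95% power claim with the between-group power at that number: about 58% at two-sided 0.01, or 79% at two-sided 0.05, for 5 mmHg and SD 12. State the sidedness, and say that the figure makes no allowance for clustering.

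The tolerable loss of about 29% may be given as well, but not as the only change. On its own it would put a back-calculated rate in place of the plan's assumption and leave standing the 95% claim for 212, which a two-sample test does not support.

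The cost is a sentence or two and a less favourable stated power. Enrolment, conduct and analysis do not change.
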